### Participants

To be part of this study, all participants should fulfill the following inclusion criteria: a) ≥ 40-year-old and ≤ 75-year-old; b) diagnosed with mild to moderate ID; c) able to participate in activities in groups of 10 people; d) able to follow an exercise program on cycle ergometer; e) able to wear an accelerometer; f) able to walk independently; g) able to understand and perform all the fitness assessments; h) have medical clearance to perform exercise; and i) the participant and his/her parent(s)/legal guardian(s) should be willing to provide written consent.

Exclusion criteria will be: a) participants diagnosed with severe or profound ID; b) atlantoaxial instability; c) inability to walk unaided and unassisted; d) contraindications to exercise; e) use of medications that may influence the participants’ response to exercise; f) inability to communicate in Spanish/Catalan; g) unable to provide written informed consent; and h) parent(s)/legal guardian(s) not willing to provide written informed consent.

### Informed consent

A rigorous process and procedure of obtaining consent for the study will be set out to allow participants to be fully informed, autonomous, and empowered to consent. Participants and parent(s)/legal guardian(s) interested in being part of the study will review the documents with a member of the research team, allowing participants to ask questions or voice concerns.

Participants will be provided with adequate time to decide on participation in the study. To be part of the study, participants and parent(s)/legal guardian(s) must sign the informed consent form.

### Randomization and blinding

After baseline assessments and obtaining participants’ and parents’/legal guardians’ written informed consents, all volunteers will be centrally randomized to one of the three study arms (the CAEP, or SIT or CG) by using a stratified random-block randomization scheme. Three factors will arrange stratification: level of ID (mild or moderate), down syndrome (yes or not) and sex (male and female). Each of the 90 participants will be assigned with a unique serial number code generated by the Statistical Package for Social Science (SPSS) v 25.0 (IBM SPSS, Chicago, IL, USA) and randomly assigned in a 1:1:1 ratio to one of the three groups (*n* = 30 each). The serial number codes will be inserted into opaque envelopes that will be opened in the presence of the participant and parent(s)/legal guardian(s).

Because of the nature of the intervention, it is not possible blinding neither participants nor the exercise scientist delivering the interventions. Researchers in charge of the outcomes assessments and statistical analysis will be unaware of the participants’ allocations.

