### Sample size

An average increase in VO_2_ peak of 0.2 L/min was reported in previous studies that implemented multi-component exercise programs for adults with ID [26, 32]. In the present study, a target increase of 0.2 L/min and a standard deviation of 0.1 L/min in VO_2_ peak has been used for sample size calculation [38]. Assuming a 95% confidence level, 5% alpha error, and 20% beta error, with a 1:1:1 ratio between groups, we will seek to recruit 24 participants per group. To allow for a drop-out rate of 20% throughout the study, a total of 90 participants, 30 participants in each group, will be required.

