### Statistical analysis

Outcome analysis will be performed blinded to group allocation. The descriptive analysis of the sample will be expressed as mean and standard deviation for continuous and normally distributed variables, meanwhile non-normal distributed variables will be presented as median and interquartile range. Categorical variables will be presented as number and percentage with their standard error. Normality and homogeneity will be tested by using Kolmogorov-Smirnov test and Levene’s test, respectively. When necessary, appropriate transformations will be applied in case of non-normal distributions.

The analysis of the data set will follow an intention-to-treat design and all randomized participants for whom baseline assessments were conducted will be included in the final analysis.

To analyze the outcomes of the study we will use linear mixed-effect models with repeated measures. We will assess changes over time (W -1; W 24; W 48) and between study arms. Appropriate post-hoc tests will be implemented to analyze within and between group differences of the study arms at each time point. Categorical variables will be analyzed using Pearson’s χ-squared or Fisher’s exact test at baseline, after intervention and follow-up period.

To examine the correlations between the different outcomes, Pearson’s correlations and multiple regression analysis will be performed.

If necessary, baseline differences between the trial arms on outcomes variables will be used as covariates and fitted as factors in the models.

Two-sided tests of statistical significance will be used in all analyses. Effects size of the interventions will be presented in addition to significance tests. Significance levels will be set at an alpha level less than 5%. Statistical analyses will be conducted using SPSS v. 25 (IBM SPSS Statistics, Chicago, IL, USA).

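### The described mixed model names none of the three randomisation strata, and its covariate rule would not admit them, so between-arm comparisons at each visit are conservative if the strata are prognostic

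*Protocol article*

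**What the plan says.** Protocol article, Randomization and blinding: participants are allocated "by using a stratified random-block randomization scheme", "randomly assigned in a 1:1:1 ratio to one of the three groups". The strata are given as "Three factors will arrange stratification: level of ID (mild or moderate), down syndrome (yes or not) and sex (male and female", which makes 2 × 2 × 2 = 8 cells for 90 people.

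Protocol article, Statistical analysis: "To analyze the outcomes of the study we will use linear mixed-effect models with repeated measures". The effects named are visit and arm: "We will assess changes over time (W -1; W 24; W 48) and between study arms". Comparisons of arms at single visits are planned explicitly: "Appropriate post-hoc tests will be implemented to analyze within and between group differences of the study arms at each time point". One sentence governs covariates: "If necessary, baseline differences between the trial arms on outcomes variables will be used as covariates and fitted as factors in the models".

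No section places ID level, Down syndrome or sex in the model, and no section says they are excluded.

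**The concern.** Stratified blocks keep the arms close to balance on the three factors, which removes part of the chance variation in the arm difference. A model without the factors still counts their contribution as residual noise. Its standard error is then larger than the true variability of the estimate, and the precision that stratification created does not reach the confidence interval.

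The conditional covariate rule does not repair this, for two reasons. It is limited to outcome variables, and the three factors are not outcomes. It is also triggered by observed imbalance, which blocking is meant to prevent. What is at stake is precision, mainly in the visit-by-visit comparisons between arms, in a trial planned around 24 evaluable participants per arm.

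**Working it through.** **Inputs from the protocol article.** Effect 0.2 L/min, SD 0.1 L/min, two-sided 5% alpha, 80% power, 24 per group, 20% dropout, 30 per group (Sample size; Statistical analysis). Eight strata, 1:1:1 (Randomization and blinding).

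**Assumed, because the article is silent.** R² is the share of variance in the analysed value that the three factors explain jointly, taken as 0.1 to 0.3. Where simulation is used, block size is 3, there are 72 completers, and the SD of the VO2 peak level is 0.4 L/min.

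**1. The plan's own sample size.** The article says "a target increase of 0.2 L/min and a standard deviation of 0.1 L/min in VO_2_ peak has been used for sample size calculation". Two-mean formula: n = 2 × (1.960 + 0.842)² × (0.1/0.2)² = 3.9, so 4 per arm, not 24. Twenty-four per arm at 80% power corresponds to SD = 0.2 / (2.802 × √(2/24)) = 0.247. The dropout step does reproduce: 24/0.8 = 30, and 3 × 30 = 90. The gap between 4 and 24 is a separate matter. It is relevant here only because at SD 0.1 power exceeds 99.99% with or without adjustment, so a power effect shows only against the nominal 80% target (SD 0.247).

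**2. Standard-error ratio.** Unadjusted/adjusted = 1/√(1 − R²). With the factors perfectly balanced, the unadjusted type I error is 2 × [1 − Φ(1.96/√(1 − R²))]. Adjusted power, if unadjusted power is 80%, is Φ(2.802/√(1 − R²) − 1.96).

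| R² | SE ratio | Unadjusted type I error | Adjusted power |
|---|---|---|---|
| 0.1 | 1.05 | 3.9% | 84% |
| 0.2 | 1.12 | 2.8% | 88% |
| 0.3 | 1.20 | 1.9% | 92% |

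Stratified allocation also steadies the unadjusted estimate, so its power ends slightly above 80%. The gap between the two analyses is therefore a little smaller than 80% against the last column; see step 4.

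**3. Arm difference in level at one visit.** Take level SD 0.4 with R² 0.3, and an independent change with SD 0.1. The unadjusted SE is √(0.16 + 0.01) × √(2/24) = 0.119. With the factors removed it is √(0.16 × 0.7 + 0.01) × √(2/24) = 0.101. Simulation with stratified blocks agrees:

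| | Model SE | Actual SD of estimate | Type I error | Power for 0.2 L/min |
|---|---|---|---|---|
| Unadjusted | 0.120 | 0.103 | 2.3% | 33% |
| Adjusted | 0.101 | 0.101 | 4.9% | 48% |

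**4. Change (arm-by-time) contrast.** A time-constant factor cancels from a within-person change unless it predicts the change.

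- Factors predict level only: SE 0.029 either way; type I error 4.9% unadjusted, 5.0% adjusted. Nothing is lost.
- Factors explain 10% of change variance: type I error 3.9% against 5.2%; power at change SD 0.247 is 81% against 84%.
- Factors explain 30%: type I error 2.0% against 4.9%; power 82% against 91%.

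**5. Which terms help.** In a fitted mixed model on one simulated data set, adding the factors as main effects cut the SE of the week-24 level difference from 0.081 to 0.072 but left the arm-by-time SE at 0.0285. In a second set of simulations, where the factors did predict change, the arm-by-time SE was 0.0449 without the factors, 0.0449 with main effects, and 0.0404 with factor-by-time interactions.

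**The case against.** The strongest reply is that this reads too much into a condensed article. The Statistical analysis section gives no full list of model terms, and an analysis plan that is not shown may include the strata. That stands against any claim that the factors are excluded: a reader might infer that, but no sentence says so. It does not dispose of the point. The article does state how covariates enter, and that rule, as published, is data-driven and does not reach the strata.

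A reader might also infer that every standard error is inflated and that power falls well below plan, even to 59% at R² 0.4. The documents do not support this:

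- The sample size is framed as a target increase, and the change contrast loses nothing unless the factors predict change.
- The 59% figure arises only if 80% power is assigned to the adjusted analysis. The Sample size section describes no adjustment, so 80% belongs to the unadjusted one. With total SD fixed, 20% dropout and blocks of 3, simulated unadjusted power stayed at 81% to 84% for R² 0.1 to 0.4, while adjusted power was 83% to 95%. Adjustment adds to planned power; its absence does not take power below plan.
- Block size is not stated, and 3 is the smallest possible with three arms. With blocks of 9 and 20% dropout, unadjusted type I error at R² 0.4 was 2.7%, against 1.2% with blocks of 3 and no dropout.

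Finally, the error is conservative: it creates no false positives, and that limits its weight.

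**Conclusion.** The point holds in a limited form. The described model names none of the stratification factors, and the one covariate rule would not bring them in. For between-arm comparisons at each visit, which the article plans, the consequence is a standard error about 1.05 to 1.20 times what it need be if R² is 0.1 to 0.3, with tests below their nominal 5%. For the change contrast the same loss arises only if ID level, Down syndrome or sex predicts the change itself.

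The R² range is an assumption with no source in the article, and the exact type I error also depends on the unstated block size and on dropout. On the stated effect and SD, no material loss of power for VO2 peak can be shown. The case for changing the plan is that analysis should match randomisation at almost no cost, not that the trial is underpowered for this reason.

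**What to change.** Replace the conditional covariate sentence, as far as the strata are concerned, with a prespecified one: ID level, Down syndrome and sex enter the primary and all secondary mixed models as fixed effects, whatever balance is observed, together with their interactions with visit. The interactions are needed because main effects alone leave the arm-by-time standard error unchanged.

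Cost: one sentence. Degrees of freedom: 3 for the main effects and up to 6 more for the interactions (3 factors × 2 post-baseline visits). Sample size, randomisation and data collection are unaffected.

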### Study intervention

The multi-component exercise programs will be delivered at the occupational day centers for adults with ID. All sessions are designed by experienced sports scientists and physiotherapists, following the American College of Sports Medicine (ACSM) and the National Strength and Conditioning Association (NSCA) guidelines [17, 39]. The different trainers in charge of delivering the interventions will undergo standardized training to ensure that the sessions offered at the various centers will be comparable. The multi-component exercise programs will include aerobic, resistance, balance and flexibility training.

Participants from the CAEP and SIT program will undergo a 24-week exercise program consisting of three sessions per week (72 exercise sessions), 90-min per session. Both groups will be divided into 3 groups; 10 participants/group and the participant-trainer ratio of 10:2. The programs will be divided within 3 phases: initial phase (week 1 to 6); improvement phase (week 7 to 16); and maintenance phase (week 17 to 24). Sessions for both groups will be matched for the total duration.

All sessions will include 10-min for standardized warm-up and cool-down exercises. Warm-up will be implemented to gradually increase the HR, body temperature, joint mobility and prepare the body of the participants for the exercises of the conditioning phase. After the conditioning phase, cool-down exercise will be performed followed by stretching exercise.

The resistance training will include a total of 22 exercises (see Additional file 1): 8 for upper-limbs (biceps curl, triceps extension, lateral shoulder raise, rotator cuff exercise); 8 for the torso (4 for lower and upper back: seated back extension, low row; reverse flies; standing high row; 2 for abdominals: side bend, seated crunch; and 2 for chest: wall push-off, standing chest press); and 6 for lower limbs (squats, hip abduction/adduction, knee extension/flexion, and calf raise).

All the exercises will be performed with yellow and red elastic bands (Thera-Band®, The hygienic Corporation, Akron, OH) or participants’ body weight. To control the intensity of the strength training, we will use the 0 to 10 points RPE OMNI-RES scale [40] designed for resistance training with elastic bands.

The intensity of the resistance training will increase during each phase (Table 1).

**Table 1 Tab1:** Intensity of the resistance training

Phase	Sets	Repetitions	Rest between sets	Intensity (RPE)
1: Initial	3	12–15	1′ to 2’	5–6
2: Improvement	3	10–15	1′ to 2’	7
3: Maintenance	3	12–15	1′ to 2’	8

Balance training is designed to challenge central and peripheral mechanisms involved in the control of movement and stability (vestibular; visual and somatosensory). The training will start with static positions on the floor, progressing from double-leg stance with feet apart and together, to semi tandem and tandem stance, and one-leg stance. Subsequently, the participants will perform the same exercises with eyes closed.

Once the participants can hold these positions (10–30 s), we will introduce balance pads and will follow the above-explained progression.

During the subsequent cycles, participants will perform progressively challenging dynamic activities which will consist of toe-to-heel walk, walking on a line, side walking, reverse walking, zig–zag walking, longer strides, tandem walking and obstacle courses with cones. These activities will be performed on different surfaces and at different elevations.

Finally, increasingly challenging dual tasks activities such as turning their head toward a visual target during walking will be introduced.

Flexibility exercises will be executed after the cool-down period of each session. We will use sustained stretches for each major muscle group targeted during the session. Active and passive static stretching exercises will be used, holding the position for 10–30-s at a point of tightness or slight discomfort [17].

Volume and intensities for warm-up, cool-down, resistance, balance and flexibility exercises will be similar for both intervention groups. The difference between the CAEP and SIT program consist in the cycling training modality.

Based on previous studies [41, 42], a training attendance ≥75% will be set as the minimum attendance rate to achieve the results expected. We will divide the participants between those who adhere and do not adhere to ≥75% of training sessions. Compliance and adherence with the exercise programs will be determined by the number of sessions attended and completed in accordance with the exercise protocols.

#### Continuous aerobic exercise program

As mentioned before, the CAEP will be based on a combination of aerobic, resistance, balance and flexibility exercises (Fig. 2). Aerobic training will be performed on cycle ergometers (Concept 2 BikeErg, Concept2 Inc., Morrisville, VT). During the program, the exercise on the cycle ergometer will start with 5-min of warm-up followed by three bouts of continuous cycling at a steady-state intensity. The length of the bouts (5 to 10-min) and intensity (55 to 85% of the HR reserve) will be progressively increased across each phase (Table 2). To ensure that the participants are exercising at the appropriate intensity, Polar M200 HR monitors (Polar Electro OY, Finland) will be worn.

**Fig. 2 Fig2:**
[figure not shown]
Sample of continuous aerobic exercise training intervention per session

**Table 2 Tab2:** Intensity and duration of the continuous aerobic exercise program

Phase	No. of bouts per session	Bout duration (min)	Intensity (HRR)
1: Initial			
Week 1 to 3	3	5	55%
Week 4 to 6	3	7	60%
2: Improvement			
Week 7 to 9	3	8	60%
Week 10 to 12	3	9	65%
Week 13 to 16	3	10	70%
3: Maintenance			
Week 17 to 20	3	10	75%
Week 21 to 24	3	10	75–85%

#### Sprint interval training program

The SIT program will consist on a combination of aerobic, resistance, balance and flexibility exercises (Fig. 3). The SIT will be performed on cycle ergometers (Concept 2 BikeErg, Concept2 Inc., Morrisville, VT). During the SIT program, exercise will start with 5-min of warm-up followed by all-out SIT bouts. The SIT group will perform bouts of 5 to 10-min of exercise consisting of 5 to 20-s all-out sprints followed by 15 to 60-s of low cadence recovery (1:3 and 1:2 work-rest ratio). The duration of the sprints and the active recovery will be modified throughout the program (Table 3). The HR of the participants will be controlled by using Polar M200 HR monitors (Polar Electro OY, Finland).

**Fig. 3 Fig3:**
[figure not shown]
Sample of sprint interval training intervention per session

**Table 3 Tab3:** Intensity and duration of the sprint interval training program

Phase	No. of bouts per session	Bout duration (min)	No. of repetitions	Work: rest ratio
1: Initial				
Week 1 to 3	3	5	15	5″ – 15”
Week 4 to 6	3	7	21	5″ – 15”
2: Improvement				
Week 7 to 9	3	8	12	10″ – 30”
Week 10 to 12	3	9	9	15″ – 45”
Week 13 to 16	3	10	8	20″ – 60”
3: Maintenance				
Week 17 to 24	3	10	10	20″ – 40”

#### Control group

The participants of the CG will continue with their activities of daily living while receiving the usual care from their centers, which exclude exercise. Participants from the CG will receive Polar M200 HR monitors (Polar Electro OY, Finland) that will be used to control changes on their activities of daily living.

They will be visited be the researchers 2 to 3 times a week, during the 6 months of the intervention program. During these visits, the researchers will interview the participants to verify that their daily routines have not been modified. Given the benefits of exercise training and for ethical reasons, participants who completed the 12 months in the CG will receive SIT program for 6 months.

### Outcome measurements

Assessments will be conducted on three occasions over 12 months: at baseline = W − 1; at the end of the intervention = W 24 (6 months after baseline) and follow-up = W 48 (6 months after the end of the intervention) (Fig. 4 shows the SPIRIT Figure).

**Fig. 4 Fig4:**
[figure not shown]
SPIRIT figure showing schedule of interventions, enrolment and assessments

During baseline assessments, personal information regarding age; sex; ID level; ID etiology; living arrangement; education; medication, smoking and alcohol habits; gross annual household income will be obtained.

All tests will be conducted during the morning at a room temperature of 22–24 °C and relative physical humidity between 55 and 65%. Participants will be fasted for at least 3 h before the scheduled visit. Additionally, participants will be requested neither consume alcohol, caffeine (coffee, soda, tea, chocolate, etc.) or vasoactive medication for 12 h before testing visit nor engage in exercise for at least 24 h before the visit to the laboratory.

#### Primary outcome measurement

##### Maximal aerobic capacity

To assess the maximal aerobic capacity, the participants will perform a cardiopulmonary exercise test on a precalibrated cycle ergometer (Excalibur, Lode, Groningen, the Netherlands), cycling at 50–60 rpm. After a 1-min period cycling at 0 W, participants will follow a 10 W/min ramp protocol until exhaustion. Peak effort of the test will be considered when the participant achieves a plateau in HR or a respiratory exchange ratio (RER) ≥ 1.1 or at volitional exhaustion.

VO_2_ peak (L/min), relativeVO_2_ peak (ml/kg/min), minute ventilation (VE) (L/min) and RER will be measured breath-by-breath with an automatic gas analysis system (Metasys TR-plus, Brainware SA, La Valette, France) equipped with a pneumotachometer and making use of a two-way mask (Hans Rudolph, Kansas, USA). Gas and volume calibrations will be performed before each test, according to the manufacturer’s guidelines. Peak values will be recorded as the highest value during the last 30-s of exercise. Participants will be monitored continuously via a 12-lead electrocardiogram (CardioScan v.4.0, DM Software, Stateline, Nevada, USA).

#### Secondary outcomes measurement

##### Anthropometric measurements

Height will be measured to the nearest 0.1 cm with a stadiometer (Seca 225, Seca, Hamburg, Germany). Weight will be measured to the nearest 0.1 kg on a digital scale (Tanita MC-780 U, Arlington Heights, IL, USA), with the participant wearing lightweight clothing and no shoes. Body mass index (BMI) will be calculated as weight in kilograms divided by height in meters squared (kg/m^2^). Body fat percentage and fat-free mass percentage will be obtained via segmental (arms; trunk and legs) bioimpedance analysis (Tanita MC-780 U, Arlington Heights, IL, USA).

With a tape measure, waist circumference will be measured three times at the midway between the lower rib and the iliac crest on the midaxillary line. Hip circumference will be measured three times at the level of greatest protuberance of the buttocks.

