**Methods:**

In this trial, ninety seniors with ID between the ages of 40 and 75 yrs. from occupational health centers from the Autonomous Region of Catalonia (Spain) will be recruited. Participants will be randomly allocated to the CAEP, SIT, and control group. Both intervention groups will train 3 days/week, 1.5 h/day over 6 months. Outcome variables will be assessed at baseline, 6 months and 12 months. The outcome variables include weight, height, body composition, cardiorespiratory fitness, muscle strength, balance, flexibility, cardiovascular parameters (blood pressure, pulse-wave velocity, pulse-wave analysis), QoL and cognitive function. The intervention effect will be determined with mixed models with repeated measures to assess changes in the outcome variables over time (baseline to month 12) and between study arms. Relationship between variables will be analyzed with appropriate regression analyses.

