## Background

Persons with an intellectual disability (ID) present with alarming levels of sedentary lifestyles or very low levels of physical activity (PA) [1–3]. In addition, they present with greater multi-morbidity than persons without ID [4].

Although a direct relationship between health problems and low levels of PA or sedentary lifestyle has been established [5, 6], a large number of people do not meet the minimum levels of PA necessary for health benefits, especially older adults [7].

This relationship is of more concern in people with ID. The lack of support as well as multiple barriers faced by persons with ID to access sport facilities or exercise programs [8–10] put them in a vulnerable situation and at higher risk for suffering chronic diseases associated to sedentarism.

The aging process in people with ID starts around 40–50 years of age [11, 12]. Aging in adults with ID is associated with low physical fitness and health problems such as osteoporosis, diabetes, musculoskeletal disorders, dementia, hypertension and peripheral arterial disease [13, 14]. In Spain, adults with ID between 40 and 45 years old are considered older adults because the frequency of suffering these illnesses is similar to that of adults older than 65 years without ID [15].

Improved medical, healthcare and more person-centered care have gradually increased the mean life-expectancy of persons with ID [16]. Therefore, alternative and innovative solutions to maintain physical function and improve health and quality of life (QoL) of people with ID should include PA and exercise training.

To achieve clinically significant health-benefits and impact on health-related physical fitness, it is important to progress exercise volume and intensity [17]. Further, to maintain functional independence, cardiovascular health, muscle strength and prevent falls, resistance training should be included in multi-component exercise programs for people with ID [17–19]. Exercise programs for people with ID should take into account these general recommendations, without forgetting that delivering PA programs tailored to the specific needs of adults with ID is challenging because they need specific support, additional encouragement, and often, they may stop exercising if any discomfort is perceived [20].

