### Setting and recruitment

Occupational day centers for adults and seniors with ID from the Autonomous Region of Catalonia (Spain) will be contacted to be part of the present study. For those centers interested in getting a more detailed description regarding the project, the research team will inform the relevant professionals at each center about the background and aims of the study.

Interested adults between the ages of 40 and 75 yrs. diagnosed with mild to moderate ID from the centers that volunteer to be part of the study, will be invited to the first meeting with their families/legal guardians and care-givers from the centers. During this meeting, the procedures of the trial, testing procedures, benefits, risks and the time required for the study will be explained. In addition, an information sheet about the research and an informed consent form for participants and parent(s)/legal guardian(s) will be distributed.

During the second visit and after the informed consent is signed, participants will be requested to bring a history of medical conditions. Participants will undergo a physical examination and complete a health screening questionnaire to disclose any pathology, contraindication and/or conditions that will preclude them from participating in exercise. Additionally, participants will complete a QoL questionnaire and the emotional and cognitive function assessments.

During the third visit, all volunteers will participate in familiarization sessions before baseline testing at the laboratory. The number of familiarization sessions will be repeated until the researcher observes that the participants are confident and able to perform all assessments correctly. Finally, during the fourth visit participants will complete the remaining assessments at the laboratory facilities. The same tests will be repeated at month 6 (end of training period) and month 12 (6 months follow-up).

Volunteers included in the present study and their parent(s)/legal guardian(s) will receive written feedback explaining the results and changes of the outcome variables at the end of the training period and at the end of the follow-up period. The participants will also be given a Polar M200 heart rate (HR) monitor (Polar Electro OY, Finland) to wear during the course of the study.

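### Body fat % and fat-free mass % are one variable, and neither alone shows which way lean mass moved; fat-free mass in kg, derivable from data already collected, should be the lean-tissue outcome

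*Protocol article*

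**What the plan says.** The protocol article, Secondary outcomes measurement, Anthropometric measurements, states: "Body fat percentage and fat-free mass percentage will be obtained via segmental (arms; trunk and legs) bioimpedance analysis". Both quantities are percentages. The article names no fat mass or fat-free mass in kg.

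The same paragraph covers body weight: "Weight will be measured to the nearest 0.1 kg on a digital scale (Tanita MC-780 U, Arlington Heights, IL, USA". Weight and both percentages therefore come from one device.

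The Abstract (Methods) lists weight separately from body composition: "The outcome variables include weight, height, body composition, cardiorespiratory fitness, muscle strength, balance, flexibility". Setting and recruitment fixes the repeat visits: "The same tests will be repeated at month 6 (end of training period) and month 12 (6 months follow-up".

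On the intervention, Study intervention says: "The multi-component exercise programs will include aerobic, resistance, balance and flexibility training". The Background gives the reason for the resistance component: "muscle strength and prevent falls, resistance training should be included in multi-component exercise programs".

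The Statistical analysis section plans linear mixed models with effect sizes for the outcomes, and Pearson correlations and multiple regression between outcomes.

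**The concern.** Two named outcomes suggest two pieces of information, one about fat and one about lean tissue. Here there is only one. If both are tested, the same result appears twice and could be read as a fat finding supported by a lean finding. In the planned analyses between outcomes, the pair gives an uninformative correlation of −1, and entering both in one regression gives perfect collinearity.

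The second issue is what the lean outcome measures. Fat-free mass % depends on both compartments. It rises when fat is lost even if lean tissue is unchanged, and it can rise when lean tissue falls. In an ageing group doing 24 weeks of progressive resistance exercise, a reader is likely to take fat-free mass as evidence on lean tissue, and the percentage does not supply that.

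**Working it through.** The documents give no body-composition values, so the starting weights and fat percentages below are assumptions for illustration. The plan has no figure on this point to reproduce.

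**Step 1: the two outcomes are complements.** Weight = fat mass + fat-free mass. Dividing by weight and multiplying by 100 gives

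fat-free mass % = 100 − body fat %.

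The same holds within each segment (arms, trunk, legs). The correlation is exactly −1.

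**Step 2: consequence for the analysis.** In a linear mixed model with an intercept, replacing y by 100 − y changes the intercept to 100 minus its old value and reverses the sign of every arm, time and arm-by-time coefficient. Variance components, standard errors, p-values and the absolute size of standardised effects are unchanged. This applies on the untransformed scale. If one of the two were log-transformed, for example, the results would differ slightly, but only because of the transformation.

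**Step 3: fat-free mass % does not fix the direction of lean change.** Assume 75 kg and 35% fat, so fat-free mass is 75 × 0.65 = 48.75 kg (65.0%).

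| Change | Weight (kg) | Fat-free mass (kg) | Fat-free mass % |
|---|---|---|---|
| Baseline | 75 | 48.75 | 65.0 |
| −3 kg fat, lean unchanged | 72 | 48.75 | 48.75/72 = 67.7 |
| −2 kg fat, −1 kg lean | 72 | 47.75 | 47.75/72 = 66.3 |
| +1 kg lean, +0.54 kg fat | 76.54 | 49.75 | 49.75/76.54 = 65.0 |

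The percentage rises by 2.7 points with no lean change, rises by 1.3 points with a lean loss of 1 kg, and stays flat with a lean gain of 1 kg.

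**Step 4: weight resolves the ambiguity.** Assume 70 kg and 35% fat, so fat-free mass is 45.5 kg, and let body fat fall to 32% (fat-free mass % from 65 to 68). Using fat-free mass (kg) = weight × (1 − body fat %/100):

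| Follow-up weight (kg) | Fat-free mass (kg) | Change (kg) |
|---|---|---|
| 65 | 44.20 | −1.30 |
| 66 | 44.88 | −0.62 |
| 66.9 | 45.49 | about 0 |
| 70 | 47.60 | +2.10 |
| 73 | 49.64 | +4.14 |

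One and the same change in the percentage is compatible with lean changes from −1.30 to +4.14 kg over these weights. Once the recorded weight is used, the answer is unique.

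**Step 5: precision of the derived value.** Weight is read to 0.1 kg (error up to 0.05 kg). If the percentage is read to 0.1 (assumption; error up to 0.05 points), the largest rounding error is 70 × 0.0005 + 0.68 × 0.05 = 0.069 kg. That is small beside the changes in Step 4.

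**The case against.** A reader might infer that the trial will be unable to say whether either programme preserved or built lean mass. The documents do not support that. Weight is a listed outcome, measured on the same device and repeated at months 6 and 12, so whole-body fat-free mass in kg can be computed at each visit. In the last row of Step 3, the lean gain would show as a weight rise of 1.54 kg at constant composition. This objection stands in full: the fault lies in the outcome definition, not in the data.

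It can also be said that lean mass is not a stated aim. The Background justifies resistance training by function, strength and falls, and the protocol measures strength, chair stands, balance and mobility directly. That is correct and limits the importance of the point. But the article does choose to name a fat-free outcome, and in the form that tracks lean tissue poorly. For its primary measure it records peak oxygen consumption both in L/min and per kg of body weight; for body composition it gives only the relative form.

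Nothing in the article says that the two percentages will be presented as independent evidence, so double reporting is a risk and not a plan. Finally, the article is condensed, and derived variables may be set out in a fuller document. That would answer a complaint about something omitted. Here the article itself fixes two outcomes and their units, and those two are redundant.

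**Conclusion.** The point holds as a flaw in the definition of one secondary outcome. Body fat % and fat-free mass % are the same variable with the sign reversed, so a test of one duplicates a test of the other, and neither alone shows the direction of lean-mass change. The identity is exact under the two-compartment model. The sizes (for example +1.3 points despite 1 kg of lean loss) rest on assumed starting values and only illustrate it.

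No information is lost for the whole body, since weight is recorded at the same visits. What is missing is a named outcome that uses it; as the article stands, an analysis in kg would be a choice made outside the stated definitions. Peak oxygen consumption as primary outcome, the sample size and the main analysis are untouched. This is a small improvement that costs almost nothing.

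**What to change.** In the anthropometric outcome definition, and in the analysis plan if there is one:

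- Name whole-body fat-free mass in kg as the lean-tissue secondary outcome, computed at each visit as weight × (1 − body fat %/100).
- Keep body fat % as the adiposity outcome.
- State that fat-free mass % will not be tested or reported as a separate result, and will not be entered with body fat % in any correlation or regression.

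The cost is a change of wording. Weight and body fat % are already collected, so no measurement, visit or sample-size change follows. This covers the whole body only. Segmental fat-free mass in kg would need segment masses, which the article does not mention; it should be added only if the device output supplies them. The definition should be settled before anyone sees results by arm.
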